### Biostatistical considerations

#### Sample size

For baseline data collection, based on predicted prevalence rates of 30% for dyslipidemia in people <30 and 45% for those ≥ 30 years of age, confidence interval of 95%, study power of 80%, attrition rate of 20%, design effect of 2% for seven age groups and two sexes, sample size was calculated to be 14280. Therefore, 15005 subjects were selected randomly from areas covered by 3 health centers. In phase 2 of TLGS, based on 5% decrease in serum cholesterol, two gender, three age groups, 5% design effect and 30% attrition rate, sample size for intervention group was calculated as 4750 subjects. Therefore, population covered by one of the 3 health centers (5630 people) selected for intervention and 9375 subjects under coverage of other two centers used as controls.

Because of the wide scope of the project and variety of the measured variables, different types of analyses are performed, depending on the type of the reports or the variables and outcomes.

Although the original of this study was based on reducing hypercholesterolemia, however, in all subjects including those less healthy or normals, changes in other risk factors, NCD, and outcomes delineated in this study will also be followed in statistical considerations.

In most of analyses we will considered each individual separately, however, for interfamilial relations we will consider intraclass correlations in analyses. It should be also mentioned that in multistage cluster random sampling procedure, each health center in district 13 was a cluster and families in three randomly selected centers were recruited. Continuous data are expressed as their measures of location and spread in total and subgroups. For qualitative and categorized continuous variables, percentages and frequency distributions are reported.

Normality of distribution of the continuous variables will be examined using histograms, measures of skewness and kurtosis, Kolmogrove-Smirnove test and sometimes Chi-square test. When log-transformed values are used, geometric means are computed. Percentiles will be used to describe the high or low values of the skewed variables. When assumptions of the parametric statistical methods are not met, nonparametric methods of their counterparts will be used. These methods also were used for analysis of variables, not originally continuous, such as attitudes, quality of life etc.

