Incidence rates of NCDs such as diabetes mellitus, angina pectoris, myocardial infarction, hypertension etc., will be estimated adjusted mainly for age and sex. Relative risks for different factors and their 95% confidence interval will be reported.

Continuous variables will be compared between intervention and control groups using student's t-test. Analysis of variance (ANOVA) will be used to compare the variables among three or more subgroups followed by appropriate post hoc test such as Tukey. To adjust the comparison by the potential confounding variables, two or three-way ANOVA will be used. In addition, analysis of covariance will be employed when adjusting for a covariate correlated with the dependent variable. To compare the proportions between two or more groups, Chi-square test of independence and Fisher exact test will be employed. Matel-Haenszel test will be used when adjustment required. To compare the data with their baseline, paired t-test and repeated measures analysis of variance or McNemar, Sign and Friedman tests will be used.

To evaluate the relationship between variables, Pearson or Spearman correlation coefficients is used Multiple regression analysis will be used to find out the relationship between variables such as blood pressure, fasting blood sugar, lipid profiles and variables regarded as independent variables such as body mass index, waist circumference, lipid profiles, age, etc.

When the outcome variable was defined as dichotomous, for instance, diabetes mellitus, hypertension, etc., multiple logistic regressions was employed to assess the relation of potential risk factors and the outcomes. Multinomial logistic regression will be used when the outcome is defined as polychromous variable, e.g., diabetes mellitus, impaired glucose tolerance (IGT) and normal. Odds ratio and its confidence interval will be reported and interpreted. Secondary outcomes (e.g., mortality, cardiovascular morbidity) will be analyzed using life table method to evaluate the association of different factors on survival time, Cox regression analysis was performed. A proportional hazards regression model will be used to evaluate potential covariability that may modify the primary and secondary outcomes. The adequacy of the models will be checked, usually, using the Hosmer-Lemeshaw statistic. In addition, ROC curve and its area under curve (AUC) will be used to compare the predictability of different fitted models.

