### Target groups and aims

A goal of NCD prevention activities should be to improve lifestyle and health of individuals by preventing or delaying the onset of NCD risk factors and associated outcomes. The primary aim of TLGS is, thus, to compare the occurrence of risk factors and outcomes in population selected for lifestyle modification with non-intervened general population in Tehran. In order to have sufficient duration to test intervention effects on risk factors and late outcomes and mortality, the study will be continued for at least 20 years. Sample size used in this study is more than many studies concerned with changes of NCD risk factors and outcomes [54,58]. In addition children and adolescents comprise more than 30% of study population and their follow up of interest in a preventive interventional study. Although lifestyle modification may alter or delay the occurrence of risk factors and outcomes, many predisposing physiology abnormalities that are caused by genetic factors and socioeconomic conditions may play important roles in these disorders. Most of these abnormalities are currently unknown. Therefore, TLGS will give opportunities to examine NCD related genetic and socioeconomic factors in study population.

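### Repeated-measures ANOVA and Friedman tests, as named, drop anyone with a missed survey although 30% attrition is planned; and a normality test should not be what chooses the method

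*Protocol article*

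**What the plan says.** All references are to the protocol article.

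- **Comparison with baseline** (Biostatistical considerations): "To compare the data with their baseline, paired t-test and repeated measures analysis of variance or McNemar, Sign and Friedman tests will be used".
- **Attrition** (Sample size): the phase 2 calculation uses "5% design effect and 30% attrition rate, sample size for intervention group was calculated as 4750 subjects". It does not say whether the 30% is the total loss or the loss per wave.
- **Schedule**: Study design sets 3-year intervals between data collections. Target groups and aims says "the study will be continued for at least 20 years".
- **Group comparison** (Biostatistical considerations): the t-test, multi-way ANOVA, ANCOVA, chi-square, Mantel-Haenszel, logistic and Cox methods are named separately. No method that uses incomplete series is named for repeated continuous measurements.
- **Normality** (Sample size): the checks are histograms, skewness and kurtosis values, Kolmogorov-Smirnov and, at times, a chi-square test. Log transformation with geometric means is foreseen. Then: "When assumptions of the parametric statistical methods are not met, nonparametric methods of their counterparts will be used". No cut-off or p-value rule is given.

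**The concern.** Two of the named methods fit this design poorly. Repeated-measures ANOVA in its classical form and the Friedman test need a value from every person at every wave in the analysis. With re-surveys every 3 years over two decades, one missed survey removes the person and all of that person's other data. The share lost grows with each wave added.

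Lost precision is the smaller cost. If attendance depends on observed earlier health, those with complete series are a selected group, and their mean change is a biased estimate of change in the cohort. A comparison of change between groups suffers most if that dependence differs by group. The Retention section itself ties retention to power and validity, and says that the obstacles to retention differed between families.

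The secondary concern is the route to rank tests. With thousands per group, a formal normality test reacts to departures that do no harm to a comparison of means. The usual rank counterparts give no covariate-adjusted effect, so an unneeded switch would give up adjustment.

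**Working it through.** **The plan's own figure.** The 4750 that carries the 30% attrition cannot be reproduced. Phase 2 states a 5% fall in cholesterol but no mean, SD, alpha or power. Nothing below depends on it except the allowance for loss: 4750 × 0.70 = 3325 people expected to remain in the intervention group.

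**Number of re-surveys.** 20 / 3 = 6.7, so six full re-surveys.

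**Two-visit tests (paired t, Sign, McNemar).** If 30% is the total loss, a baseline-to-visit pair keeps 70%:
- intervention: 5630 × 0.70 = 3941
- control: 9375 × 0.70 = 6562

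The 3941 exceeds the 3325 allowed for.

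**All-wave tests (repeated-measures ANOVA, Friedman).** The complete share is the product of the retention at each wave. The attendance rates are assumptions, because the article gives none.

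| Assumption | Complete at all six re-surveys | Of 5630 |
|---|---|---|
| 30% lost in total, no other missed visits | 70% | 3941 |
| 90% attend each survey, independently | 0.90^6 = 53% | 2992 |
| 85% attend each survey, independently | 0.85^6 = 38% | 2123 |
| 80% attend each survey, independently | 0.80^6 = 26% | 1476 |
| 30% lost at each wave | 0.70^6 = 12% | 662 |

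At 90% attendance any single baseline pair still keeps 90%, while the all-wave test falls to 53%. In every row but the first, the complete series fall below 3325.

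**Normality check.** Gamma samples with skewness 0.2 were simulated, with mean and SD estimated from the sample.

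| n | Plain Kolmogorov-Smirnov, cut-off 1.358/√n | Lilliefors, cut-off 0.886/√n |
|---|---|---|
| 5630 (full intervention group) | about 45% rejected | 98% rejected |
| 938 (5630 / 6 sex-by-age cells) | 1% rejected | 32% rejected |

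The article does not say which cut-off applies. At n = 5630 and skewness 0.25, plain Kolmogorov-Smirnov rejected 82%.

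**Does the t-test need the switch?** Two groups of 3941 and 6562 were drawn from the same gamma distribution, 2000 runs each. The rejection rate at nominal 5% was 4.8% at skewness 0.5, 5.2% at skewness 1 and 4.9% at skewness 2. The test keeps its size well beyond the skewness that a formal test would flag.

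**The case against.** The strongest reply is that the sentence on baseline comparisons concerns change within persons. The intervention-versus-control comparison has its own methods, and none of them needs six complete re-surveys. This stands. A reader might infer that the main group contrast rests on 53% or 12% of the cohort; the article does not support that.

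Three further replies also stand:
- The paired t, Sign and McNemar tests lose only people who lack one of two visits. They do not belong with the all-wave tests.
- The 30% is already in the sample size, and 3941 exceeds 3325. A reader might infer that the study is underpowered for its baseline-to-visit comparisons; under a 30% total loss it is not, by the plan's own allowance.
- The normality rule is broader than a test. Histograms, skewness and kurtosis values would show that a skewness of 0.2 is trivial. A reader might infer that a Kolmogorov-Smirnov p-value sends variables to rank tests; no such rule is written.

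On retention by group, both groups have the same 3-yearly examinations and annual calls (Baseline measurements, Outcome measurements), and the Retention section describes study-wide recovery of non-attenders. Differential attendance is possible, because only the intervention area has the added classes and clinics, but the article does not show it.

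Finally, an article condenses, and detailed missing-data handling may sit in a plan that is not shown. Its absence is therefore no fault. That does not answer the point about what is stated: two complete-series methods are named for a study that expects substantial loss.

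**Conclusion.** The point holds in a limited form. Repeated-measures ANOVA and Friedman, in classical form and run across waves, match the planned attrition poorly. Over six re-surveys the usable share runs from 70% down to 12%, depending on what the 30% means and on assumed attendance. The article does not settle either, and it does not say that all waves would enter one test.

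Bias is conditional. It arises if attendance depends on observed earlier health, and the article gives no dropout mechanism.

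The normality point is a risk rather than a stated rule. It applies if a formal test drives the choice at full group size, and it is much weaker within sex-by-age cells.

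Both points merit a change in wording because a better method on the same data is available at little cost.

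**What to change.** **Continuous outcomes.** Replace repeated-measures ANOVA and Friedman with a likelihood-based mixed model:
- baseline and all available surveys in the outcome vector, so that people who never return still contribute their baseline value;
- group, survey and their interaction, with covariates stated in advance, such as age and sex;
- random effects for person and family, in line with the intraclass correlation that the article already foresees within families.

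The model is valid when dropout depends on observed values, provided that it is correctly specified.

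**Binary outcomes.** Use mixed logistic regression, or GEE with inverse-probability weights for attendance. Unweighted GEE is generally not valid when dropout depends on earlier observed values.

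**Attrition.** State whether the 30% is per wave or in total.

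**Normality.** State that formal normality tests will not decide the method for the group comparison. List in advance the skewed variables to be log-transformed, and use robust standard errors.

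**Cost.** Wording in the analysis section and standard software; no new data. Analysis and reporting become slightly more complex, and the weighted GEE needs a model for attendance.

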### Management

#### Organization

##### TLGS Unit

The unit is located in eastern part of Tehran city. A four story building composed of a laboratory, admission, information, examination rooms, nutrition, and social worker units. It has a Manager and additional staff to carry out the details of study protocol and includes dietitians, social workers, recruitment coordinators, electrocardiogram technicians, laboratory personals, physicians, nurses, data collectors and others.

##### TLGS Steering committee

The Principle Investigator, Program Coordinators, additional researchers, manager and head of sections in TLGS Unit meet at least twice monthly. This committee is responsible for approval of epidemiologic and biostatistic design, policies and decisions, and oversees the administrative aspects of the TLGS Research Group.

Subcommittees consist of members of the Research group, develop detailed policies and procedures, make recommendations to TLGS steering Committee and help to prepare presentations and write design and publications. The following subcommittees are active throughout the study: Nutrition, Physical activity, Smoking, Outcomes, Obesity, Metabolic disorders, Program coordinators and School intervention.

##### Central resource units

these units are located in the main building of Research Institute for Endocrine Sciences. They comprised of Central Biochemical Laboratory, Nutrition unit, Biostatistics unit and others. These units back-up and monitor activities in the TLGS Unit, help for quality control, biostatistical design, analysis and data storage and processing.

### Data Management

#### TLGS Unit

A network of micro-computers helps to collect paperless data. In rare conditions, data collected on paper forms are double-entered into the computers.

#### Central resources

Electronic copies of the newly entered and update data in TLGS Unit is transmitted via telecommunications link to the Central Resource units, where they are compiled into the TLGS master database. Weekly edit reports are performed and out-of-range, inconsistent values and discrepancies within forms are re-assessed.

## Discussion

Major NCDs comprise the most difficult health threatening issues in the third millennium and epidemics of these conditions have been considered [49]. Coronary artery disease (CAD) is one of the leading causes of morbidity and mortality all over the world [50], affecting not only industrialized, developed countries, but also populations of developing countries, which undergo significant lifestyle changes as a result of rapid industrialization. Premature CAD and cardiovascular risk factors have been shown to have a high prevalence in Iran [50,51]. Therefore identification of people at risk of developing coronary atherosclerosis is an important public health issue in the Iranian population as in other populations [50].

The etiology of CAD has been established to be multifactorial with both genetic and environmental components [52]. Traditional risk factors, such as the male sex, increasing age, hypertension, diabetes mellitus, family history of premature CAD, elevated plasma levels of LDL-C and low HDL-C have been shown to be independent predictors for CAD in numerous studies performed in different setting [53-57].

Few studies focusing on the prevalence of NCD risk factors in children adolescent, adults, and elderly have been conducted in Iran [5,9-11,58,59]. Recognizing the need to obtain relevant data on prevalence and distribution of the factors responsible for excess NCDs in Iranian population, the Endocrine Research Center of Research Institute for Endocrine Sciences initiated the Tehran Lipid and Glucose study in 1999. The baseline data of this project reported high prevalence of NCD risk factors particularly of high total cholesterol, low HDL-C and high waist to hip ratio [2]. Since an effective strategy for lifestyle modification is the cornerstone of population approach to the NCD risk factors, the second phase of this study was designed for intervention aiming at reducing NCD risk factors and outcomes.

### Target groups and aims

A goal of NCD prevention activities should be to improve lifestyle and health of individuals by preventing or delaying the onset of NCD risk factors and associated outcomes. The primary aim of TLGS is, thus, to compare the occurrence of risk factors and outcomes in population selected for lifestyle modification with non-intervened general population in Tehran. In order to have sufficient duration to test intervention effects on risk factors and late outcomes and mortality, the study will be continued for at least 20 years. Sample size used in this study is more than many studies concerned with changes of NCD risk factors and outcomes [54,58]. In addition children and adolescents comprise more than 30% of study population and their follow up of interest in a preventive interventional study. Although lifestyle modification may alter or delay the occurrence of risk factors and outcomes, many predisposing physiology abnormalities that are caused by genetic factors and socioeconomic conditions may play important roles in these disorders. Most of these abnormalities are currently unknown. Therefore, TLGS will give opportunities to examine NCD related genetic and socioeconomic factors in study population.

### Lifestyle intervention

Overweight and obese individuals and those who are less physically active are more likely to develop NCDs [60]. Western-like diets and an increasingly sedentary lifestyle, with consequent increase BMI, are associated with development of NCD risk factors in different populations. Therefore, lifestyle modification aimed at reducing weight help to prevent NCD risk factors and outcomes [61]. In addition prevention and quit smoking cigarettes are considered effective in prevention of NCDs [24].

In addition to beneficial effects of lifestyle modification in prevention of NCD risk factors, and outcomes, this strategy has been effective in reducing morbidity and mortality in individuals affected by NCDs [8]. It has been shown that losing ≥ 7% of body weight appear to improve insulin sensitivity and glycemic control in both individuals with IGT [62] and type 2 diabetes [63,64]. Modest increase in exercise improves insulin sensitivity and promotes long-term maintenance of weight loss. So that physical activity of 150 minutes per week of moderate activity, such as walking, is recommended by the Centers for Disease Control and Prevention and the American College of Sport Medicine [65].

Although the feasibility of behavioral intervention for prevention of type 2 diabetes and some other NCDs have been demonstrated [66,67], World Health Organization does not consider this as suitable intervention for NCD prevention. Therefore, except for programs which help people to cope with stress, we did not include behavioral intervention in TLGS.

Iranian population like other developing country residents are exposed to rapid changes in their lifestyle because of increasing availability of processed food, high fatty food consumption and decreasing physical activity [1]. This so called "nutrition transition" is accompanied by changes in epidemiology of disorders and shift from communicable to NCDs. In addition, complications of both under-and over nutrition are present concomitantly. There is no doubt that these changes contribute to increase the prevalence of obesity, sedentary, hypertension, diabetes, dyslipoproteinemia and consequently may elevate the prevalence of NCDs morbidity and mortality in Iranian populations.

### Place of intervention

The intervention sites in TLGS are widespread throughout the community, with emphasis on schoolchildren and adolescents. Over the last few decades, the concept of food has changed from a means of nourishment to a symbol of lifestyle [68-70]. Increased dietary fat intake can contribute more calories than other macronutrients, so exposing children to tasteful low-fat foods would be an important component of early prevention programs. On the other hand, high fiber diets might protect against obesity and CVDs by lowering insulin levels [71,72]. Some evidence supported the use of multifaceted school-based interventions to reduce the risk factors of non communicable diseases and obesity [71-75]. Thus, in TLGS, nutrition intervention in schools included educational programs, parental involvement and healthy school buffet.

## Conclusion

The incidence of NCDs is increasing worldwide; these diseases result from major risk factors including smoking, hypertension, dyslipidemia and impaired glucose homeostasis levels [76]. Various countries in the world are initiating community-based programs to control the modern epidemics of non-communicable diseases. These interventional approaches may differ according to the community, socioeconomic, cultural and health settings.

The TLGS has been designed in Iran as a prospective cohort study aimed at following up participants for at least 20 years longitudinally for monitoring the trend of NCD risk factors. The interventional phase of the study is designed for lifestyle modification of the general population with special emphasis on the risk factors found to be most prevalent in the baseline study. This project has been approved and founded by the National Council of Scientific Research of the I.R. Iran as a National Research Project. The experience of the TLGS in Iran may support the idea that a well-planned, fully evidence-based, and well-developed national community-based program may be affordable to prevent non-communicable disorders in developing countries undergoing nutritional transition.

TLGS also provides a large database for future health studies on this population, for example a large clinical trial cohort is under way to assess the effects of several measures (i.e., education, dietary modification, physical activity, and metformin) on preventing the development of diabetes mellitus in this population. In addition, further biochemical, immunologic and genetic studies using sera bank and DNA bank of this study may shed more light in the etiology, pathogenesis and alterations in body composition related to NCDs and their risk factors.

